### Participant withdrawal criteria

The mean and systolic blood pressure will be recorded every 15 minutes in both the GTN and Control Groups until the intervention ends. If any participant in either the GTN Group or Control Group develops hypotension (defined as a > 30% drop in systolic blood pressure from baseline) and/or any sudden increase in the oxygen requirement with an increase in the methemoglobin levels (determined by blood gas analysis), they will be removed from the study. Participants can withdraw from the study at any point.

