### Study endpoint

The primary endpoint of the study is radial artery diameter. After obtaining informed consent from a patient's parent, images of the radial artery will be obtained from the infant's wrist using a portable ultrasound machine. The diameter of the radial artery will be measured using a linear, high-frequency hockey stick probe (6 - 113MHz) with the Philips EPIQ CVx Diagnostic Ultrasound system.

Measurements will be obtained in the short-axis plane of the distal forearm, medial to the border of the styloid process of the radius and at the point with maximal pulsation of the radial artery, with the wrist at a 45º angle.^(16)^ The point will be marked to guide the intervention and ensure coverage of the site over the peripheral artery, which will be measured postintervention. The operator will be an experienced neonatologist blinded to the study group. Measurements will be obtained in both radial arteries at baseline before application of the GTN patch/bandage with no patch and at 30 minutes, 45 minutes or 60 minutes after application.

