### Outcomes

#### Primary outcome:

the primary outcome will be the change in the postintervention radial artery diameter from baseline. This will be compared between the GTN and Placebo Groups.

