#### Safety outcomes:

in this study, the side effects of topical GTN, such as hypotension and methemoglobinemia, will be assessed.

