### Sample size

We aim to recruit 60 patients (15 in each arm: 1 control and 3 GTN arms) over 12 months, which is achievable given that we expect approximately 250 eligible patients to be admitted to the neonatal ICU each year.

Justification of the sample size is based on the desire to demonstrate that reasonable vasodilation with GTN patch application is achievable in our target study population. We assume that the measures of the radial artery diameter in study participants will have a mean of 0.76mm without treatment and a common within-group standard deviation of approximately 0.18mm, as observed in a reference study of neonates aged 0 - 6 months.^(12)^ With a sample size of 15 for each group (1 control and 3 GTN patch groups), the margin of error around the corresponding estimated population mean diameters is less than 1 mm, and an omnibus one-way ANOVA would have more than 80% power to determine whether GTN patch application increases the radial artery diameter when the minimum mean of the treatment group differs from that of the control group by approximately 0.19mm (alpha = 0.05). Analyses based on the change from baseline, which is our primary outcome, are expected to be more powerful than analyses assessing the cross-sectional diameters, and the detectable cross-sectional difference of 0.19mm corresponds to an approximate 25% increase from the estimated baseline value, which is of the order previously observed in children aged 0 - 2 years receiving subcutaneous injections of GTN,^(11)^ and substantially less than that observed after patch application in children aged 2 - 8 years (average increase of 40% in the radial artery diameter after 30 minutes and an increase of 70% after 1 hour).^(10)^ Furthermore, power will be increased by extending the assessment of GTN-induced vasodilation to an ANCOVA that reduces residual variation by adjusting for key demographic/clinical correlates of arterial diameter.

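### The withdrawal rule takes infants out of the study, not only off the intervention, when a safety outcome occurs, so the primary outcome can be lost for reasons related to treatment

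*Protocol article*

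**What the plan says.** Under Participant withdrawal criteria, the rule applies to any infant in either group who "develops hypotension (defined as a > 30% drop in systolic blood pressure from baseline) and/or any sudden increase in the oxygen requirement"; the second trigger also needs a rise in "methemoglobin levels (determined by blood gas analysis), they will be removed from the study". It speaks of the study and does not mention stopping the patch or bandage as a separate step.

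The same section gives the monitoring schedule: "The mean and systolic blood pressure will be recorded every 15 minutes in both the GTN and Control Groups until the intervention ends".

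Under Outcomes, "the primary outcome will be the change in the postintervention radial artery diameter from baseline". Under Study endpoint, diameters are taken "at baseline before application of the GTN patch/bandage with no patch and at 30 minutes, 45 minutes or 60 minutes after application", so each infant has one post-baseline scan. Under Safety outcomes, "the side effects of topical GTN, such as hypotension and methemoglobinemia, will be assessed". Table 3 plans ANCOVA for the primary outcome and mixed effects models of patient trajectories for blood pressure and methemoglobinemia.

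The Sample size section takes 15 infants per arm straight into the power statement ("With a sample size of 15 for each group (1 control and 3 GTN patch groups"), with no stated allowance for loss. The only text on data after withdrawal is under Ethics and dissemination. It concerns withdrawal by a parent or guardian: data already collected are kept unless the family objects, and nothing more is collected.

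**The concern.** The rule makes leaving the study depend on an event after randomization that the study drug may cause and that the trial sets out to measure. If an infant meets it before the scan, the primary outcome is never taken. The infants left in the GTN arms may then no longer be comparable with the control infants.

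Two of the protocol's own objectives are touched. One is to confirm safety, yet recording stops at the event, so its further course is not captured. The Justification of the dose section says levels wane with a half-life of about 30 minutes after the patch is removed, so that course is of interest. The other is to inform the choice of application time, yet the chance of being removed before the scan can grow with the assigned duration.

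An analysis plan cannot recover measurements that the protocol tells staff not to take.

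**Working it through.** **1. Timing.** Assume that checks start 15 minutes after application and that the scan takes place at the assigned time.

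| Assigned time | Checks before the scan | Number |
|---|---|---|
| 30 min | 15 | 1 |
| 45 min | 15, 30 | 2 |
| 60 min | 15, 30, 45 | 3 |

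Every arm has at least one check at which an infant can be removed without a primary outcome, and the number rises with duration.

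**2. The plan's own power.** Inputs from the Sample size section: four groups of 15, SD 0.18 mm, difference 0.19 mm, alpha 0.05, omnibus one-way ANOVA. Take means of 0, 0.19, 0.19 and 0.19 mm relative to control.
- Noncentrality = (n_control × n_GTN / N) × (difference/SD)² = (15 × 45 / 60) × (0.19/0.18)² = 11.25 × 1.114 = 12.53.
- With 3 and 56 degrees of freedom, power is 0.830. The stated figure of more than 80% is reproduced.

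**3. Power if only GTN infants are lost.** Control stays at 15 and there is no bias.

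| Per GTN arm | Infants lost of 45 | Noncentrality | Power |
|---|---|---|---|
| 15 | 0 | 12.53 | 0.830 |
| 14 | 3 | 12.31 | 0.821 |
| 13 | 6 | 12.07 | 0.810 |
| 12 | 9 | 11.80 | 0.798 |

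Loss alone takes power below 0.80 only when 9 of 45 (20%) are gone.

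**4. Possible bias in the GTN mean.** The documents give neither a removal rate nor a link between a systemic reaction and local dilation, so both are assumed. Let p be the share of GTN infants removed and rho the correlation between removal risk and dilation, with no control infants removed. For a normal latent risk cut at z, the upper-p point:

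bias = −rho × SD × phi(z) / (1 − p)

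- p = 2%: z = 2.054, phi = 0.0484. At rho = 0.3, −0.3 × 0.18 × 0.0484 / 0.98 = −0.003 mm. At rho = 0.7, −0.006 mm. This is 1-3% of 0.19 mm.
- p = 5%: z = 1.645, phi = 0.1031. Bias −0.006 to −0.014 mm (3-7%).
- p = 10%: z = 1.282, phi = 0.1755. At rho = 0.3, −0.011 mm. At rho = 0.7, −0.025 mm (6-13%).
- rho = 0: bias 0 at every p. At rho = −0.3 and p = 10%: +0.011 mm, so the sign reverses.

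The SD of 0.18 mm is cross-sectional. A smaller SD of the change from baseline would shrink these figures in proportion.

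**5. Is the loss repaired elsewhere?** The clause under Ethics and dissemination covers parental withdrawal only and adds no later measurement. The monitoring committee section counts hypotension and methemoglobinemia but does not keep removed infants in follow-up. No text provides for a scan after removal.

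**The case against.** The case against making much of this is substantial, and most of it stands.

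- **Frequency.** The Justification of the dose section reports no hypotension or methemoglobinemia in the pediatric studies, and infants with hypotension, shock or unstable vital signs are excluded. Removals may be rare or absent. However, the Introduction says those studies were very small and did not include neonates, so a low rate cannot be taken as known.
- **Direction.** A reader might infer that the rule strips out the infants who responded most to GTN. The documents do not support this. The triggers are systemic, the primary outcome is the local diameter, and no text links the two.
- **Methemoglobin.** A rise alone does not remove an infant; it must accompany a sudden rise in oxygen requirement. Table 1 lists the blood gas as postintervention, so this trigger may fall close to the scan and need not cost the primary outcome.
- **Blood pressure model.** A reader might infer that the model must understate the fall. That is not shown. The reading that triggers removal is recorded, and a correctly specified likelihood-based mixed model can handle dropout that depends on observed values. Event counts also survive. What is lost is the course after the event.
- **Power.** A reader might infer that losing one infant per arm breaks the power claim. That holds only if a control infant is lost too (0.798 with 14 in all four arms), which does not fit a concern about GTN-related removal.
- **Analysis plan.** Analysis sets and missing-data methods are commonly set there. That answers a complaint about analysis detail, but not a protocol rule that ends data collection.

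**Conclusion.** The point holds as a design defect of unknown size. Followed as written, the rule can make the primary outcome missing for a treatment-related reason, can do so unequally across the three durations, and ends safety recording at the event.

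Whether any bias follows, and in which direction, cannot be told from the documents. It is zero if no infant is removed or if removal is unrelated to dilation. The range of 0.003-0.025 mm (1-13% of 0.19 mm) rests entirely on the assumed 2-10% removal of GTN infants, the assumed correlation of 0.3-0.7, no control removals and the cross-sectional SD. The effect of lost numbers alone on power is slight.

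The reason to act is that the missing measurements cannot be recovered later and that preventing the loss is cheap.

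**What to change.** Amend Participant withdrawal criteria so that stopping the study intervention and leaving the study are separate events. The clinical triggers and the infant's management stay unchanged. For an infant who meets a trigger:

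- keep the infant in the study;
- obtain the postintervention ultrasound where the infant's condition allows, and record its time relative to application and removal;
- continue the planned safety recording, and say until when, because blood pressure recording is currently tied to the end of the intervention;
- analyse the infant in the randomized group.

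State that only withdrawal by a parent or guardian ends data collection.

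The cost is a few sentences and, for any affected infant, measurements that were already planned. The downside is small: these diameters reflect a shorter exposure than assigned, which should be reported.

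In the same amendment, reconcile the two definitions of hypotension. Participant withdrawal criteria require a systolic fall of more than 30%, while Data and safety monitoring counts a fall of 30% or more.

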### Outcomes

#### Primary outcome:

the primary outcome will be the change in the postintervention radial artery diameter from baseline. This will be compared between the GTN and Placebo Groups.

#### Secondary outcomes:

the secondary outcomes will be the postintervention cross-sectional radial artery diameter in the ipsilateral limb and the percentage change in the radial arterial diameter in the ipsilateral limb from baseline. Postintervention absolute and percentage changes in the radial arterial diameter in the contralateral limb from baseline will also be assessed.

#### Safety outcomes:

in this study, the side effects of topical GTN, such as hypotension and methemoglobinemia, will be assessed.

### Participant timeline

The study schedule is shown in table 1.

Duration of participant participation: 30 minutes to 1 hour.

### Sample size

We aim to recruit 60 patients (15 in each arm: 1 control and 3 GTN arms) over 12 months, which is achievable given that we expect approximately 250 eligible patients to be admitted to the neonatal ICU each year.

Justification of the sample size is based on the desire to demonstrate that reasonable vasodilation with GTN patch application is achievable in our target study population. We assume that the measures of the radial artery diameter in study participants will have a mean of 0.76mm without treatment and a common within-group standard deviation of approximately 0.18mm, as observed in a reference study of neonates aged 0 - 6 months.^(12)^ With a sample size of 15 for each group (1 control and 3 GTN patch groups), the margin of error around the corresponding estimated population mean diameters is less than 1 mm, and an omnibus one-way ANOVA would have more than 80% power to determine whether GTN patch application increases the radial artery diameter when the minimum mean of the treatment group differs from that of the control group by approximately 0.19mm (alpha = 0.05). Analyses based on the change from baseline, which is our primary outcome, are expected to be more powerful than analyses assessing the cross-sectional diameters, and the detectable cross-sectional difference of 0.19mm corresponds to an approximate 25% increase from the estimated baseline value, which is of the order previously observed in children aged 0 - 2 years receiving subcutaneous injections of GTN,^(11)^ and substantially less than that observed after patch application in children aged 2 - 8 years (average increase of 40% in the radial artery diameter after 30 minutes and an increase of 70% after 1 hour).^(10)^ Furthermore, power will be increased by extending the assessment of GTN-induced vasodilation to an ANCOVA that reduces residual variation by adjusting for key demographic/clinical correlates of arterial diameter.

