### Statistical methods

Table 3 gives a description of the timing and method of assessment of the efficacy and safety parameters. The ultrasound operator and examiner will be blinded to the study.

**Table 3 t3:** Timing and method of assessment of the efficacy and safety parameters

		Measured by	Analysis
Primary efficacy outcome			
	Change in postintervention ipsilateral radial arterial diameter from baseline	Ultrasound at the site of cannulation measured at time of randomization of glyceryl trinitrate/placebo patch and 30, 45 or 60 minutes postintervention	ANCOVA
Secondary outcomes			
	Cross-sectional radial artery diameter in the ipsilateral limb	Measured postintervention by ultrasound	Linear regression
	Percentage change from baseline in radial arterial diameter in ipsilateral limb	Ratio of the postintervention to baseline radial arterial diameters as measured by ultrasound	Linear regression
	Change in the radial artery diameter in the contralateral (no intervention) limb from baseline	Difference and ratio of the radial artery diameter measured at baseline and postintervention	Mixed effects regression modeling of radial artery diameters in both limbs.
Safety outcomes			
	Blood pressure	Systolic blood pressure monitored every 15 minutes	Mixed effects regression modeling of patient trajectories
	Methemoglobinemia	Monitoring of the oxygen requirement and a blood gas analysis if the oxygen requirement increases	Mixed effects regression modeling of patient trajectories

ANCOVA - Analysis of covariance.

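### The primary ANCOVA of change should name baseline ipsilateral diameter as a covariate, and the expected power gain from change scores needs a stated correlation or SD of change

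*Protocol article*

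**What the plan says.** Under Primary outcome, the article states that "the primary outcome will be the change in the postintervention radial artery diameter from baseline". Table 3 (Statistical methods) repeats this for the treated limb, "Change in postintervention ipsilateral radial arterial diameter from baseline", and its analysis column gives the single word ANCOVA. The only description of the covariates is in the Sample size section, which speaks of an "ANCOVA that reduces residual variation by adjusting for key demographic/clinical correlates of arterial diameter".

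The same section makes three separate statements about power:

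- For cross-sectional diameter, "an omnibus one-way ANOVA would have more than 80% power to determine whether GTN patch application increases the radial artery diameter" when the smallest treated-arm mean "differs from that of the control group by approximately 0.19mm (alpha = 0.05"). This assumes "a common within-group standard deviation of approximately 0.18mm".
- "Analyses based on the change from baseline, which is our primary outcome, are expected to be more powerful than analyses assessing the cross-sectional diameters".
- The covariate adjustment will raise power further.

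No pre-post correlation and no SD of change is given. Table 3 assigns linear regression, with no baseline term, to "Cross-sectional radial artery diameter in the ipsilateral limb" and to the ipsilateral percentage change. The Study endpoint and Data collection methods sections have both radial arteries measured at baseline in each infant.

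**The concern.** A change score already removes much of what is stable in an infant. Weight or gestational age may predict the size of an artery and yet say little about how far it dilates over 30 to 60 minutes. Adjusting a change score for correlates of level may therefore gain less than the article suggests. Baseline diameter behaves differently. Unless the pre-post correlation is very high, change depends on the starting value, and adjusting for that value removes residual variance that subtraction leaves in or adds.

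The stake is precision. With 15 controls, some chance difference in baseline diameter is to be expected, and a change score without baseline in the model carries part of it into the estimate. Also, the only power figure is for an outcome that is not primary. Power for the actual primary outcome rests on an expectation with no number behind it.

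**Working it through.** **Inputs.** From the Sample size section: four arms of 15, SD 0.18 mm, difference 0.19 mm, alpha 0.05, omnibus F test. The pre-post correlation ρ is not in the document, so it is varied as an assumption. Baseline and postintervention SDs are taken as equal.

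**The plan's own figure.** Put all three GTN arms 0.19 mm above control. The grand mean is then 0.1425 mm above control, and the sum of squared deviations is 0.1425² + 3 × 0.0475² = 0.0271. The noncentrality is 15 × 0.0271 / 0.18² = 12.53. With 3 and 56 degrees of freedom, power is 83.0%. The stated figure of more than 80% reproduces.

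**Change score without baseline in the model.** SD of change = 0.18 × √(2(1 − ρ)). This is below 0.18 only if 2(1 − ρ) < 1, that is, ρ > 0.5.

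**Change score with baseline as a covariate.** Residual SD = 0.18 × √(1 − ρ²), with 3 and 55 degrees of freedom.

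| Assumed ρ | SD of change (mm) | Residual SD with baseline (mm) | Power without baseline | Power with baseline |
|---|---|---|---|---|
| 0 | 0.255 | 0.180 | 50.7% | 82.9% |
| 0.3 | 0.213 | 0.172 | 67.5% | 86.6% |
| 0.4 | 0.197 | 0.165 | 74.9% | 89.4% |
| 0.5 | 0.180 | 0.156 | 83.0% | 92.7% |
| 0.7 | 0.139 | 0.129 | 97.2% | 98.8% |

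The ratio of the adjusted to the unadjusted variance is (1 − ρ²) / (2(1 − ρ)) = (1 + ρ)/2. Baseline adjustment therefore cuts variance by 35% at ρ = 0.3, 25% at 0.5 and 15% at 0.7.

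**What other covariates could do.** To bring the change score back to the cross-sectional variance, they must explain a share 1 − 1/(2(1 − ρ)) of the variance of change. That is 1 − 1/1.4 = 29% at ρ = 0.3 and 1 − 1/1.2 = 17% at ρ = 0.4. The threshold of 0.5 is thus not strict once covariates are used.

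**Chance imbalance.** For 45 against 15 infants, the standard error of the baseline difference is 0.18 × √(1/15 + 1/45) = 0.054 mm. An imbalance of one standard error moves the unadjusted change estimate by (ρ − 1) × 0.054 mm. In size this is 0.038 mm at ρ = 0.3, 0.027 mm at 0.5 and 0.016 mm at 0.7, or about 20%, 14% and 8% of the 0.19 mm effect.

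**The case against.** Taken together, the wording on covariates and the bare entry in Table 3 might lead a reader to infer that the plan adjusts for demographic factors in place of baseline. The documents do not support that. The phrase is a general one in a sample-size paragraph, not a closed list. Baseline is a usual ANCOVA covariate, and a fuller list may stand in a document not shown. If baseline is already intended, the low-power column does not apply.

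Nor does the power statement fail as written. The figure above 80% is cross-sectional, reproduces, and does not depend on ρ. The gain from change scores is only described as expected, and no sample size rests on it. The condition ρ > 0.5 belongs to that sentence, not to the one on covariates.

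Low correlations are an assumption made here. The same marked site is measured twice, 30 to 60 minutes apart, with the same plane and wrist angle, so ρ above 0.5 is plausible. At 0.7 the difference in power is small. If dilation is proportional to size, correlates of diameter would also predict absolute change to some extent.

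Finally, chance imbalance might be read as bias. Under randomisation it is not: the change-score contrast is unbiased, and its standard error already reflects such imbalance.

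All of this stands, and it limits the point to one of specification and precision. It does not remove it. The article does characterise the covariates and builds a power statement on them. Baseline diameter is named nowhere, and the gain claimed for the primary outcome has no correlation or SD of change behind it.

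**Conclusion.** The point holds as an inexpensive improvement, not as an error that undermines the trial. The primary model as described does not name its most useful covariate, and the expectation about change scores is conditional on a quantity the document does not give. With baseline in the model, calculated power is essentially at or above the cross-sectional 83% for every ρ from 0 upward (82.9% at ρ = 0, the trivial loss being the one degree of freedom), so the expectation no longer needs ρ above 0.5. Without it, power for change falls below 80% at ρ of 0.3 to 0.4, unless other covariates explain a fair share of the change. In the more plausible range of 0.5 to 0.7, the gain from baseline is a 25% to 15% cut in variance.

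These figures rest on equal pre and post SDs, all three GTN arms shifted by 0.19 mm, and assumed values of ρ.

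**What to change.** In the Sample size section and in Table 3, specify that the primary ANCOVA of change includes baseline ipsilateral diameter as a covariate, alongside any demographic or clinical covariates. Add the same term to the linear regressions of postintervention ipsilateral diameter and of ipsilateral percentage change. With identical covariates, the regression of postintervention diameter then gives the same treatment contrast as the primary analysis, so it should not be presented as separate evidence.

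Either state the assumed pre-post correlation or SD of change with its source, or qualify the statement that change is more powerful as depending on it (above about 0.5 if baseline is not in the model).

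The cost is one degree of freedom and a few words. The measurement is already taken, so no new data are needed.
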